### Randomization and allocation concealment

Stratified-block randomization would be applied into the study, which will take each center as a stratification factor. Each eligible participant will be randomly assigned to either the intervention group or control group according to 1:1 equal proportion rule. The sequence of random allocation will be generated using the PLAN sentences of the statistical software SAS 9.3 (SAS institute Inc., Cary, NC, USA), by an independent statistician who will not be involved in this trial from the Center of Evidence Based Medicine, FJTCM. Also, the sequence of random allocation will be concealed to outcome assessors and the statistical analyst. Then, the eligible participants will be informed of their allocation result by the project manager via telephone after their baseline information has been assessed, and the therapists (including acupuncturist and cognitive therapists) will be notified of the allocation and arrange the allocated treatment directly for the patient.

### Blinding

In this trial, both the outcome assessors and the statistical analyst will be blinded to the randomization allocation and will not be involved in performance of the interventions. It will be, nevertheless, impossible to blind the participants, acupuncturists, and cognitive therapists since they will perform the interventional protocols. In the meantime, a specified project manager will be assigned to be in charge of the random allocated sequence and blind code of allocation, in which the intervention group or control group will be replaced by the letter A or B. Random parameters would be kept in the blind codes, using sealed opaque envelopes to conceal random allocation. Unblinding will only occur once all the outcome data collection is completed at 36 weeks.

### Ethical issues

This protocol has been approved by the Ethics Committee of FJTCM Subsidiary Rehabilitation Hospital (approval number: 2013KY-005-01), Guangdong Province Traditional Chinese Medical Hospital (approval number: B2014-020-01), the First Affiliated Hospital of Jinan university (approval number: (2014) Ethical review approval documents 25th), Traditional Chinese Medicine Hospital of Xinjiang Uygur Autonomous Region (approval number: 2013XE005), Affiliated Huashan Hospital of Fudan University (approval number: (2014) Interim review 262th), Zhongshan Hospital of Traditional Chinese Medicine (approval number: 2014ZSZY-LLK-002), and ShiyanTaihe Hospital (approval number: 2014001 Research review meeting 2nd). Each participating center will receive approval from the local institutional review board. Prior to study, signed informed consent will be obtained from each participant. The names of seven ethical bodies are listed in Additional File 1.

### Baseline tests

Descriptive data will be collected before randomization. The descriptive data includes gender, age, height, weight, nationality, education level, employment status, clinical syndrome (left or right hemiplegia), and the type, frequency, and location of the stroke at diagnosis. The National Institute of Health Stroke Scale, an 11-item evaluation tool to assess stroke severity, will be applied at baseline to determine whether the two groups are consistent before the intervention [30]. All subjects will be assessed with the following measures: the severity of cognitive impairment will be assessed using the Mini-Mental Status Examination (MMSE), as well as the Montreal Cognitive Assessment (MoCA); attention function will be measured with the Test of Attentional Performance (TAP); memory function will be tested with the Wechsler Memory Scale-Revised in Chinese (WMS-RC); executive function will be evaluated with the Stroop test, as well as the Trail Making Test; motor function will be measured with the Fugl-Meyer Motor Assessment Scores; activities of daily living (ADL) will be assessed with the Modified Barthel Index (MBI); and quality of life will be evaluated with the 36-Item Short Form Health Survey (SF-36). Moreover, the functional condition of the brain is examined by using a resting-state functional magnetic resonance imaging (fMRI) and event-related potentials (ERP).

### Intervention

The interventional group will receive a therapeutic regimen of TCM rehabilitation and conventional treatment, while the control group will only receive CT and conventional treatment. The conventional treatment consists of health education, conventional medical therapy, and routine rehabilitation training. The treatments will be performed five times per week, over 12 weeks. For quality management, all procedures performed by the healthcare staff participating in this study will be standardized, including in the study protocol, treatment methods, and assessments.

### Basic treatment

All participant will receive basic treatments following the Chinese Medical Association’s *Guidelines for the Prevention and Treatment of Cerebrovascular Disease in China (2007)* [31] and *Guidelines for Chinese stroke rehabilitation* [32]*.* Based on these guidelines and the patient’s condition, the treating physician will manage each case, including the use of drugs, stroke risk factor prevention, and rehabilitation therapies, as well as post-stroke comorbidity management including anticoagulant therapy, blood pressure, anti-platelet aggregation, heart disease, blood sugar, and lipid management.

### Health education

All the participants will receive an informational brochure with basic knowledge on stroke, based on the *Out of the Misunderstanding of Stroke Patients*’ *Rehabilitation* (the bestseller books for health education after stroke from the Chinese Association of TCM) [33]. In addition, a health lecture is offered to participants in the hospitals, covering various topics on stroke rehabilitation, including: the definition of stroke; the type, prevention, etiology, and pathogenesis of stroke; the concept of stroke rehabilitation; the importance of early rehabilitation; best practices in stroke rehabilitation; and nursing care.

### Cognitive training

All the patients will receive CT based on the 2010 National Stroke Foundation’s *Clinical Guidelines for Stroke Management* [34]. The intervention group will receive CT and acupuncture therapy simultaneously. The therapists will tailor the treatment in accordance with each patient’s assessment results, including different aspects of CT (attention, memory, orientation, visual spatial ability, execution, or calculation and so on). Furthermore, the level of difficulty will be based on patient’s progress. The period of treatment will be sustainable for 12 weeks, at 30 minutes per day for five days a week.

### Acupuncture therapy

The intervention group will be treated on two acupuncture points (Baihui (DU20) and Shenting (DU24)). The acupoint-location method is based on bone proportional cun. Bone proportional cun is mainly marked as the primary landmarks by using joints on the surface of the body; the length between the two joints will be discounted for a certain amount of discretion in order to determine the location of the acupoints. Baihui (DU20) is located on the head, 5 B-cun superior to the anterior hairline, on the anterior median line; or when the ears are folded, Baihui (DU20) is located at the midpoint of the connecting line between the auricular apices. Shenting (DU24) is located on the head, 0.5 B-cun superior to the anterior hairline, on the anterior median line.

Acupuncture will be performed by acupuncturists who are TCM licensed, and have at least three years of experience. The acupuncture procedure starts with the patient in the sedentary or supine position. After acupoint area sterilization, the acupuncturist’s left hand should fix the skin of the stimulus area, and the right hand should hold the disposable sterile acupuncture needle (Huatuo brand, model 0.30 mm × 25 mm, Suzhou Medical Appliance Factory, China). Then, the needle is inserted into the acupoints subgaleally from the front to the rear along the scalp, at an angle of 10 to 20 °, to a depth of approximately 25 to 35 mm. Following insertion, stimulation of the acupuncture point is applied until the *de qi* sensation is achieved, which means that patients experience a certain feeling with a mixture of sourness, numbness, distension, and pain from the acupuncture. The acupuncturist will use the manipulation technique with rapid twirling performed for two to three minutes every 10 minutes, at a frequency of 180 to 300 times/min. Meanwhile, CT will be performed constantly for 30 minutes throughout the acupuncture therapy. Following the treatment session, the needles will be withdrawn, and a dry sterilized cotton ball will be slightly pressed the holes of needles to avoid bleeding. The treatment will be given once a day for five times a week, lasting for 12 continuous weeks.

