### Sample size

The sample size calculation is based on the improvement of MMSE scores, which is used as the primary effect indicators to estimate. According to the similar published articles [29], the mean difference in MMSE scores before and after treatment is three points, with a standard deviation of 1.5. According to our pilot study, a therapeutic regimen of TCM rehabilitation (CT + acupuncture) can probably improve the MMSE by 3.52 points on average compared to the control group. Improvement will be measured according to the same size of the estimation formula:1$$ \mathrm{n}=2\left[{\left({u}_{\alpha }+{u}_{\beta}\right)}^2{\sigma}^2\right]/{\delta}^2 $$

With a type I error of 5 % (α = 0.05) and 90 % power (β = 0.10), it is estimated that a sample size of 173 participants per group will be required. Considering a 20 % dropout rate during the study, a minimum of 416 total participants is needed to reach the target 208 participants per group.

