### Statistical methods

All data will be analyzed using SAS version 8.2 (SAS institute Inc., Cary, NC, USA) by an independent blinded statistician. A statistical significance level of 0.05 will be used. For statistical description, continuous variables will be presented for each group using the mean ± standard deviation for normal distribution, and median and interquartile range for non-normal distribution. Categorical variables will be presented by using proportions with their standard error. In order to compare the primary and secondary outcomes between groups, measured at baseline, post-intervention and post-follow-up, the t-test or Mann–Whitney U test will be used for continuous variables and the Pearson chi-squared or Fisher’s exact test will be used for categorical variables. Non-parametric tests, Pearson chi-squared test, or Fisher’s exact test will be used for expressing changes in effect sizes of primary and secondary outcomes between groups before and after treatment, and during the follow-up period (at 12 weeks and 24 weeks).

To adjust the confounding influence if necessary, a general linear model or linear regression will be applied for dependent continuous variables, and a logistic regression model for dependent categorical variables. The analysis of the primary outcome will be expressed by using full analysis set with the principle of intention-to treat and the per-protocol set. The analysis of the secondary outcomes will be performed using the per-protocol set. The analysis of AE will be undertaken by using a chi-square test or Fisher’s exact test. Lastly, the economic evaluation will be assessed using cost-effectiveness analysis. Missing data will be imputed by the last observation carried forward rules.

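### Acupuncture is given in one arm only, by an unstated number of operators, while the sample size and named tests assume independent patients; if outcomes vary by operator, the standard error may be too small and power may be below 90%

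*Protocol article*

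**What the plan says.** All in the protocol article:

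- **Study design, Intervention, Cognitive training.** Both arms receive cognitive training. Only the intervention arm also receives acupuncture.
- **Acupuncture therapy.** "Acupuncture will be performed by acupuncturists who are TCM licensed, and have at least three years of experience". Treatment is five times a week for 12 weeks, so 60 sessions per patient. The number of acupuncturists, their caseloads, and whether one operator treats a patient throughout are not stated.
- **Sample size.** An independent two-sample formula, n = 2(u_α + u_β)²σ²/δ², is applied "With a type I error of 5 % (α = 0.05) and 90 % power (β = 0.10"), and "it is estimated that a sample size of 173 participants per group will be required". No design effect appears.
- **Statistical methods.** The comparison is introduced with "In order to compare the primary and secondary outcomes between groups, measured at baseline, post-intervention and post-follow-up" and uses a t-test or Mann–Whitney U test for continuous variables. A linear model is reserved for confounding, if needed. Neither provider nor centre is named as a term.
- **Randomization and allocation concealment.** Allocation is 1:1, stratified by centre. There are seven centres.

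**The concern.** Acupuncture here is manual, and the described technique leaves room for the operator: ranges for depth (25 to 35 mm), angle (10 to 20°) and twirling rate (180 to 300 per minute), with stimulation continued until a sensation is reported. Patients treated by the same hands may therefore have correlated outcomes. Any such correlation from acupuncture exists in the intervention arm only, which makes the design partially nested.

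The formula and the named tests have no place for it. Stratifying by centre does not remove it, because an operator effect shifts one arm of a centre and not the other. The Discussion hopes for wider use of the therapy in clinical and community settings. A conclusion of that reach extends to acupuncturists outside the trial, and their variation then belongs in the standard error of the treatment difference. At stake are the width of the interval for the primary MMSE comparison, its false-positive rate, and the stated power.

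**Working it through.** **1. Reproduce the stated size.** The inputs are "the mean difference in MMSE scores before and after treatment is three points, with a standard deviation of 1.5" and a regimen that "can probably improve the MMSE by 3.52 points on average compared to the control group". Taken literally, δ = 3.52 and σ = 1.5 give 4 per group. The difference of the two figures, 3.52 − 3 = 0.52, comes close to the stated number:

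n = 2 × (1.960 + 1.2816)² × 1.5² / 0.52² = 174.9, so 175 against the stated 173.

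This uses two-sided α = 0.05; a one-sided test gives 143. The value 0.52 is thus an inference, not a figure in the article. The match shows that 173 contains no allowance for clustering. At 173 per group:

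- SE = 1.5 × √(2/173) = 0.1613
- power = Φ(0.52/0.1613 − 1.960) = 89.7%

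**2. Add operator clustering in one arm.** Let k be the number of acupuncturists and ICC the share of outcome variance lying between them. Both are assumptions: k = 7, 14 or 28 (1, 2 or 4 per centre) and ICC = 0.01 or 0.05.

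- Patients per operator: m = 173/k
- Design effect, intervention arm: DE = 1 + (m − 1) × ICC
- Variance inflation of the difference: V = (DE + 1)/2
- Correct SE = 0.1613 × √V
- Actual type I error of the nominal 5% test = 2[1 − Φ(1.960/√V)]
- Power of a test using the correct SE = Φ(0.52/SE − 1.960)

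| k | ICC | m | DE | V | SE | Type I error | Power |
|---|---|---|---|---|---|---|---|
| any | 0 | – | 1.00 | 1.000 | 0.1613 | 5.0% | 89.7% |
| 28 | 0.01 | 6.2 | 1.05 | 1.026 | 0.1634 | 5.3% | 88.9% |
| 28 | 0.05 | 6.2 | 1.26 | 1.13 | 0.1714 | 6.5% | 85.9% |
| 14 | 0.01 | 12.4 | 1.11 | 1.057 | 0.1658 | 5.7% | 88.0% |
| 14 | 0.05 | 12.4 | 1.57 | 1.284 | 0.1827 | 8.4% | 81.2% |
| 7 | 0.01 | 24.7 | 1.24 | 1.119 | 0.1706 | 6.4% | 86.2% |
| 7 | 0.05 | 24.7 | 2.19 | 1.593 | 0.2036 | 12.0% | 72.4% |

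Starting from exactly 90% (0.52/SE replaced by 3.2415/√V) gives 73% in the last row instead of 72.4%. These are normal approximations. They ignore the few degrees of freedom that a handful of operators would leave.

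**3. Allow for the omitted centre term.** Because allocation is balanced within centres, a t-test that ignores centre overstates the variance. If a share ρ of the variance lies between centres, the ratio of true to assumed variance is about 1 + (m − 1) × ICC/2 − ρ. With ρ = 0.05 (assumed):

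- ICC 0.01: 1 + 0.057 − 0.05 = 1.01 for k = 14, and 1 + 0.026 − 0.05 = 0.98 for k = 28
- ICC 0.05: 1 + 0.284 − 0.05 = 1.23 for k = 14, and 1 + 0.593 − 0.05 = 1.54 for k = 7

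At the low ICC the two errors roughly cancel. At the higher ICC they do not.

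**The case against.** A reader might infer that a small group of acupuncturists treats the whole arm, so that the standard error is definitely too small and the 90% definitely overstated. The documents do not support that. No number of operators, caseload or ICC is given, and several points weigh against it:

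- **Standardisation.** The article fixes the two points, the needle and the ranges of technique, requires licensed staff with a minimum of experience, and trains all staff on standard procedures. This may make the ICC small, though it cannot be assumed to be zero.
- **Rotation.** Over 60 sessions a patient may meet several operators. The operator effect would then be diluted, and the design effect above would not apply as written.
- **Centre.** Omitting centre errs in the conservative direction, so the net direction is uncertain at low ICC. This stands, but a chance cancellation does not justify the test, and adding centre to the model removes the offset.
- **The null.** If acupuncture has no effect in anyone's hands, there is no operator variance from it and the test keeps its level. Inflation requires operator effects that differ but average zero over a wider population of operators. That is a choice of inferential target; the Discussion's aim of wider use makes it reasonable, not compulsory.
- **Effect size.** On the literal 3.52 points, power is about 100% in every row. The unclear effect size is a larger problem for the power statement than clustering. The standard error and type I error columns do not depend on it.
- **Unseen documents.** A statistical analysis plan or case report form may already deal with providers. What remains is that the article itself names a formula and tests that assume independence.

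**Conclusion.** The point holds conditionally. The structure is clear from the article: one arm is exposed to operators, and neither the formula nor the named tests allow for it. Whether this matters depends on an ICC above zero, on several patients per operator with limited rotation, and on a conclusion meant to extend beyond the trial's own acupuncturists.

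Under the assumed inputs the consequence runs from negligible (5.3% type I error, 88.9% power) to material (12%, about 72 to 73%). The material end needs one acupuncturist per centre and an ICC of 0.05, and nothing in the article establishes either. The material supports a pre-stated sensitivity analysis and a qualified power statement. It does not show that the primary test is invalid, and making a nested model primary would be debatable.

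**What to change.** - Record the acupuncturist's code at each session. The study design table already lists treatment recording during weeks 1–12, so this would be one field. If it is not collected at the time, the question may not be answerable later.
- Include centre as a factor in the MMSE model.
- Pre-state a sensitivity analysis with a partially nested mixed model: a random acupuncturist effect in the intervention arm only, arm-specific residual variance, and small-sample degrees of freedom. State how it will be adapted if operators rotate.
- Keep 416 and describe the 90% power as assuming negligible operator clustering. At 0.52 points, the number per arm for 90% power would range from 180 (28 operators, ICC 0.01) to 455 (7 operators, ICC 0.05). That range is too wide to justify resizing without data on operators.

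The cost is one data field, one extra model, and possibly a wider interval in the sensitivity analysis. Treatment and recruitment are unchanged.

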### Follow-up

After the 12-week treatment period, there is an outpatient 24-week follow-up period. The medical staff will follow up on the participants via telephone. Each participant is contacted once every four weeks, keeping record of the medications and rehabilitation therapies. On the final week of the follow-up period (24 weeks post-intervention), participants will be referred for clinical evaluation in order to assess their functional status, including cognitive function, quality of life, and ADL.

### Outcome measures

In this study, all the primary and secondary outcomes measures will be tested at baseline (−2 to −1 week) and after the intervention period (12 weeks). After follow-up (36 weeks), the cognitive function, quality of life, and ADL outcomes (MMSE, MoCA, SF-36, and MBI) will also be evaluated. All outcome assessments will be independently performed by experienced and blinded assessors. A summary of all the measures in the trial is shown in Table 1.

### Primary outcomes

#### Mini-Mental State Examination

The Mini-Mental State Examination (MMSE), was first introduced by Folstein *et al*. in 1975 [35], and we will use the revised Chinese MMSE version [36]. It is a brief 30-point questionnaire, divided into 10 items: time and place orientation, short-term memory, attention and calculation, recall, language skills, repetition, complex commands, reading, writing, and copying of pentagons. When the resulting MMSE is 24 points or less, this means that the patient may suffer from some degree of cognitive impairment. The total score of the individual items demonstrates the recent severity of cognitive impairment.

### Secondary outcomes

#### Montreal Cognitive Assessment

The Montreal Cognitive Assessment (MoCA) [37] is a 30-point test that covers eight cognitive domains, including: visual spatial ability and execution, naming, memory, attention, language, abstraction, delayed recall, and orientation. Given the MMSE’s limitation in detecting early dementia [38], the MoCA evaluates participants who suffer from cognitive complaints. The revised Chinese MoCA version will be used in this trial.

#### Test of Attentional Performance

The Test of Attentional Performance (TAP, Version 2.3) [39], a computer-aided standard neuropsychological test, is used to assess attention disorders. Four of its sub-tests were chosen for this trial: alertness for reaction, general anticipation (which belongs to general attention); Go/No Go, and incompatibility for selective attention and divided attention, which is essential in every attention assessment. The TAP measures reaction time, and the number of errors and omissions. The available TAP in Chinese will be used in this study.

#### Wechsler Memory Scale-Revised in Chinese

Memory will be evaluated using the Wechsler Memory Scale (WMS). The Wechsler Memory Scale-Revised in Chinese (WMS-RC) will be used [40]. The test consists of three sub-functions (11 sub-tests): long-term memory (including information and orientation, forward recite digit (1 to 100), backward recite digit (100 to 1), and accumulation), short-term memory (including visual recognition, picture recall, visual reproduction, associative learning, touch, and comprehension memory), and immediate memory (including digit span). The results of the WMS-RC are expressed by memory quotient (MQ). We will collect MQ values and all sub-test values for analysis.

#### The Trail Making Test and the Stroop test

Executive function will be measured with the TMT and the Stroop test. The TMT is one of the most popular neuropsychological tests and provides information on visual search and executive functions [41]. It consists of part A and part B (TMT-A and TMT-B). In part A, the participants are asked to make lines from 1 to 25, while in part B, subjects should make lines from 1 to 25 while alternating between circles and squares [42]. This study also adopts the Color-Word Stroop interference test using E-prime to assess subjects’ executive function. Subjects were asked to judge if the color of the top row in the computer screen corresponds to the color name written at the bottom row, and press the left or the right button, respectively [43].

